### AIM 2. Evaluate the efficacy of the integrated intervention of ISS-SBDOH for monitoring, facilitating and improving adherence to ART

We hypothesize that the ISS-SBDOH arm will have significantly higher mean adherence to ART than the UC arm. GLMM will be used modeling adherence to ART across the contact periods. An arm (ISS-SBDOH or UC) dummy variable will be included in the model to test if the level of adherence is different between the two arms. If the distributions are substantially skewed, we will evaluate categorized clinical cut-off values using generalized estimating equation (GEE) analysis.^95^ For possible non-linear relationships between outcomes and time, we will use generalized additive mixed model (GAMM). The trend of adherence changes before and after 16 weeks will be compared. In addition, we will evaluate group differences in demographics (e.g., gender) and control for these variables in modeling. We also hypothesize that the use of ISS-SBDOH will be associated with lower levels of non-adherence (e.g., fewer single missed doses, a shorter maximum duration of taking no doses) than the UC arm over time. We will make full use of machine learning and data mining methods, including classification and regression trees (CART), random forests, XGBoost, Generalized Additive Models, to identify non-adherence patterns in the data. We will use GLMM/GAMM to model adherence between ISS-SBDOH and UC arm over time to determine if it differs between arms. The GAMM modeling will graphically show the change trend over time. We will also evaluate the distribution of DTEs and their changes over time in the ISS-SBDOH arm. We hypothesize that the differences in adherence between the ISS-SBDOH and the UC arms will be sustained during the 10-week post-intervention period. GLMM/GEE and GAMM will be used to model adherence between the two arms, including parameterization that can distinguish the 16-week trial and 12-week follow-up periods.

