### Randomization

Randomization will take place after the baseline assessment and before the intervention begins. The UC arm is chosen as the control condition because it meets ethical and moral requirements to attempt treatment. Eligible patients will be randomized to one of the two conditions using a stratified urn randomization procedure to increase the likelihood of balanced allocation of prognostic variables at baseline. We will stratify by two factors: (i) single/multiple tablet regimen, and (ii) detectable/undetectable viral load at baseline through a 2 × 2 factorial stratification, to assign them into intervention arm or UC arm within each of the four cells. Randomization is implemented electronically through REDCap.

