### AIM 3. Evaluate the efficacy of the ISS-SBDOH intervention for improving virologic outcome and reducing high risk sexual activity and STIs

We hypothesize that the participants in the ISS-SBDOH arm will have a low level of viral load and reduced high-risk self-reported sexual activity and frequency of detectable STIs compared to the UC arm. GLMM and GAMM will be used to model viral load of patients and frequency of detectable STIs in the ISS-SBDOH arm and the UC arm across the contact periods (baseline and follow-ups) to evaluate an $$\:arm\times\:time$$ interaction. We also hypothesize that the differences in viral load, and level of high-risk sexual activity and frequency of detectable STIs between the ISS-SBDOH and the UC arms will be sustained during the 12-week post-integrated intervention follow-up period. GLMM/GEE and GAMM will be used to model the viral load, level of high-risk sexual activity, and frequency of detectable STIs between the two arms including parameterization that can distinguish the 16-week intervention phase and 12-week sustainability phase.

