### Sample size calculation

Sample size calculation and power analysis were conducted based on the primary and secondary end points. For Aim 1, 55 subjects to be recruited in the ISS-SBDOH arm and 55 in the UC arm enable us to obtain stable point estimates and test the hypotheses for acceptability of the intervention program using one sample binomial approach. For the frequency and timeliness of SBDOH intervention and level of challenges, group sample sizes of 55 in the ISS-SBDOH arm and 55 in the UC arm will enable us to detect a difference as small as 0.5 in a continuous outcome (a medium Cohen’s effect size) with 80% power, and a significance level of 0.05 using a two-sided two-sample t-test. For Aim 2, using repeated measures analysis with intra-subject correlation of 0.1, a type I error of 0.05, a type II error of 0.2 (or 80% power), and average number of available data points 3.5, out of 5 data points (baseline, weeks 4, 8, 12, 16), 55 subjects in each of the two arms will enable us to detect a difference as small as 0.29 in standardized unit of the outcomes (e.g., adherence to ART) between the two arms, which is statistically and clinically meaningful. For Aim 3, for the binary outcome variable of viral suppression, using repeated measures analysis with similar set-up as Aim 2, the sample size of 55 participants in each of the 2 arms will be able to detect a 9% difference (or an odds ratio of 2.7) between the 2 arms (assuming 85% viral suppression at week 16 for control arm) and this effect size is considered clinically meaningful. Thus, the planned sample size should be sufficient for the proposed analyses.

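### On its natural reading, the Aim 2 arm test averages the pre-randomization baseline into the treatment effect, shrinking it to 71–80% of its post-baseline size and losing power

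*Protocol article*

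**What the plan says.** All references are to the Protocol article.

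- **Aim 2, data in the model:** "GLMM will be used modeling adherence to ART across the contact periods".
- **Aim 2, test:** "An arm (ISS-SBDOH or UC) dummy variable will be included in the model to test if the level of adherence is different". No arm-by-time term is named for this test.
- **Aim 3, meaning of the term:** the corresponding model runs "across the contact periods (baseline and follow-ups", and there an arm-by-time interaction is named.
- **Sample size calculation, Aim 2:** the detectable difference of 0.29 standardized units rests on 55 per arm, an intra-subject correlation of 0.1, 80% power and an "average number of available data points 3.5, out of 5 data points (baseline, weeks 4, 8, 12, 16".
- **Randomization, timing:** "Randomization will take place after the baseline assessment and before the intervention begins".
- **Aim 2, covariates:** "we will evaluate group differences in demographics (e.g., gender) and control for these variables in modeling".
- **Randomization, strata:** "We will stratify by two factors: (i) single/multiple tablet regimen, and (ii) detectable/undetectable viral load at baseline". Aim 2 does not mention these factors. The Aim 1 ratings model lists regimen type and viral load among its covariates.

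**The concern.** Baseline adherence is measured before anyone is allocated, so the expected difference between arms at that visit is zero. If the visit is an outcome row and the test is one constant arm coefficient, that coefficient is a weighted average of zero and the post-baseline effect. The estimate is then too small as a measure of what the intervention does, and the test loses power on a primary outcome.

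Adding arm-by-time terms without further definition does not solve this. With baseline as the reference visit, the arm dummy becomes the difference at baseline, which is not a treatment effect. In either case the test needs a defined post-baseline contrast.

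A smaller point lies in the same paragraph. Adjustment is tied to group differences seen in the data. After randomization these are chance differences, so the covariate set, and with it the reported model, would depend on the data.

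**Working it through.** **Inputs from the documents:** n = 55 per arm, correlation ρ = 0.1, type I error 0.05, power 80%, difference 0.29 SD, 3.5 of 5 points available on average. **Assumptions:** a two-sided test (the Aim 2 text does not give sidedness), compound symmetry, unit variance, and the same shift at every post-baseline visit.

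**Step 1. The plan's own figure.** For m points per person, the variance of a person's mean is v = (1 + (m − 1)ρ)/m, and the detectable difference is (1.960 + 0.842) × √(2v/n).

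With m = 3.5, v = 1.25/3.5 = 0.357 and √(2 × 0.357/55) = 0.114, which gives 2.802 × 0.114 = 0.319. The stated 0.29 is not reproduced, and power at 0.29 is 72%. Changing one input comes close: a one-sided test gives 0.283, all five points 0.283, and ρ = 0 gives 0.286. This mismatch is a separate matter. What counts here is that the calculation gives the full difference to every point, baseline included.

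**Step 2. Dilution.** If k of the m points are post-baseline, the expected arm coefficient is 0.29 × k/m.

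- (a) Complete data: 0.29 × 4/5 = 0.232.
- (b) 3.5 points, baseline always observed: 0.29 × 2.5/3.5 = 0.207.
- (c) 3.5 points, all visits equally likely to be missing: 0.29 × 2.8/3.5 = 0.232.

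**Step 3. Power.** Power = Φ(effect/√(2v/n) − 1.96).

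- Baseline averaged in: effect 0.29k/m, v = (1 + (m − 1)ρ)/m.
- Post-baseline visits only: effect 0.29, v = (1 + (k − 1)ρ)/k.
- Post-baseline visits with baseline as covariate: effect 0.29, v = (1 + (k − 1)ρ)/k − ρ².

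Case (a), averaged in: v = 1.4/5 = 0.28, SE = 0.1009, 0.232/0.1009 = 2.30, power 63%. Post-baseline only: v = 1.3/4 = 0.325, SE = 0.1087, 0.29/0.1087 = 2.67, power 76%. With covariate: v = 0.315, SE = 0.1070, power 77%.

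Case (b), averaged in: SE = 0.1140, 0.207/0.1140 = 1.82, power 44%. Post-baseline only: v = 1.15/2.5 = 0.46, SE = 0.1293, power 61%. With covariate: v = 0.45, power 62%.

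| Case | Expected coefficient | Averaged in | Weeks 4–16 only | Baseline as covariate | Post-baseline effect needed for 80% if averaged in |
|---|---|---|---|---|---|
| (a) | 0.232 | 63% | 76% | 77% | 0.35 |
| (b) | 0.207 | 44% | 61% | 62% | 0.45 |
| (c) | 0.232 | 53% | 65% | 66% | 0.40 |

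The last column is the detectable difference for m points multiplied by m/k, for example 0.319 × 3.5/2.5 = 0.447.

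**Step 4. Check by simulation.** Case (b) was simulated with generalized least squares (600 replicates, Monte Carlo error about 2 points). The mean coefficient was 0.207 and power 45% with baseline averaged in, against 62% for post-baseline visits only and 62% with baseline means constrained equal.

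**Step 5. Higher correlation (assumption; the documents give only 0.1).** At ρ = 0.5 the formulas give 35% against 70% with baseline as covariate in case (a), and 27% against 62% in case (b).

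**The case against.** The strongest reply is that no sentence says baseline is averaged into the arm effect. The gloss on contact periods comes from Aim 3, where the same sentence goes on to an arm-by-time interaction. Aim 2 also plans to model adherence over time, to compare trends before and after week 16, and to separate the trial and follow-up periods. A detailed analysis plan, not shown here, may define another contrast. This lowers the certainty. It does not remove the problem: the planned split is at week 16, nothing in Aim 2 separates baseline from treatment, and the only efficacy test named there is the arm dummy.

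The size also depends on which visits enter. If weeks 20 and 28 were included and the effect persisted (both assumptions), the dilution would be 6/7. Power would be about 78% (v = 1.6/7, effect 0.249) against about 86% (v = 1.5/6). The loss is smaller but still there.

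Four stronger readings are tempting and are not supported:

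- *Any use of baseline as an outcome row is an error.* It is not. A model that constrains the baseline means to be equal keeps that row and loses nothing (62% against 62% in the simulation).
- *A strong predictor is being wasted.* At the protocol's correlation of 0.1, baseline as a covariate adds only about one point of power beyond dropping it from the outcomes. The larger gains need correlations that the documents do not give.
- *Leaving out the stratification factors dilutes the effect.* Aim 2 is silent on them in a condensed article and does not exclude them. Their absence does not dilute a linear arm effect, and the power cost cannot be computed because the documents do not say how much variance they explain.
- *The fallback for skewed data is a data-driven switch.* The text says "If the distributions are substantially skewed, we will evaluate categorized clinical cut-off values", so the fallback is declared in advance. Its criterion and cut-off are details that an analysis plan commonly supplies.

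On covariates, the wording could mean only that demographics are described and then adjusted for, since no significance screen is stated. It does link adjustment to group differences, so it should be tightened, but no loss has been computed for it.

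**Conclusion.** The point holds as an inference from three sections read together: Aim 2, Aim 3 and the sample size text. On that reading, the arm coefficient recovers 71–80% of a post-baseline effect of 0.29 SD. Power falls by about 13 to 18 points at the protocol's correlation of 0.1: from 76–77% to 63% with complete data, and from 61–62% to 44% with 3.5 points and baseline always observed. These figures assume a two-sided test, compound symmetry and a constant effect over weeks 4–16. The loss is larger at higher correlations, which are an assumption.

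A reader might infer that the trial's estimate is certain to be biased toward zero. The documents do not go that far, because a contrast that excludes baseline remains possible. Importance is moderate to high, since adherence is a primary outcome. Confidence is moderate.

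**What to change.** 1. State that the primary Aim 2 test is the average arm difference over weeks 4, 8, 12 and 16. Use baseline adherence as a covariate, or keep baseline in the model with its mean constrained equal across arms. If arm-by-time terms are used, write out this post-baseline contrast.
2. In the Aim 2 power statement, count only post-baseline visits as carrying the effect, and state the sidedness.
3. Replace adjustment for observed group differences with a covariate set fixed in advance. Adding regimen type and baseline viral load detectability is recommended, since both are known at randomization, but it is not needed to cure the dilution.

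The cost is a change of analysis wording and a rerun power calculation, with no new data. The sample size text implies that baseline adherence is collected. The narrative list of baseline assessments does not name it and the schedule figure is not available here, so the sponsor should confirm this.

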## Outcomes

### Primary outcome

(i)Acceptability of the integrated intervention will be measured at baseline, and around week 4, 8, 12, and 16, evaluated by quantitative measures interviews. The items in the quantitative measure will be rated on a five-point Likert scale ranging from very strongly disagree to very strongly agree. Acceptability will be measures in terms of: overall satisfaction (would recommend to friend, would use outside of study setting, satisfied with system), utility, and specific items such as helpfulness and convenience. In addition, we will ask participants to rate items specific to the ID-Cap system (comfort of wristband, comfort receiving text messages).(ii)Frequency and timeliness of SBDOH intervention, level of challenges of SBDOH in HIV treatment will be measured at baseline, and around week 4, 8, 12, 16, 20, and 28. We will collect SBDOH measures, such as economic stability (e.g., food security), health (e.g., gap in health coverage), neighborhood and built environment (e.g. transportation needs), social and community context (e.g., violence, and criminal justice involvement), and substance and alcohol use, sexual behavior, and other health related behaviors. Challenges of SBDOH will be measured as the count of SBDOH issues one is facing, and the degree of each issue (e.g., low/medium/high with housing challenge determined by nurse or care coordinator) with summary scores. Frequency and timeliness of SBDOH intervention are measured as number of sessions, and time to first, and subsequent sessions, if applicable, from baseline, and others. This information will also be collected when intervention is triggered by the monitoring system.(iii)Adherence to ART measured by ID-Cap system for 16 weeks.(iv)Self-Reported Medication Adherence [34]. We will use a widely used measure of percent of prescribed dose taken during the preceding seven days. We will also measure patterns of dosing (e.g., patterns of consecutive missed doses in the past two weeks).

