### Statistical analyses

We will use α < 0.05 as the significance level for statistical testing, and will use appropriate corrections (e.g., Bonferroni correction) for multiple comparisons to ensure that the effective type I error remains at 0.05 level. Statistical analyses will be conducted on an intention-to-treat sample using the SAS and R statistical software.

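### Aim 2 is stated and sized as a difference in mean adherence, but a skewness clause brings in unnamed cut-offs without saying which result decides

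*Protocol article*

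**What the plan says.** In the Protocol article, section AIM 2, the hypothesis is: "We hypothesize that the ISS-SBDOH arm will have significantly higher mean adherence to ART than the UC arm". It is tested through an arm indicator in a generalized linear mixed model (GLMM). The section continues: "If the distributions are substantially skewed, we will evaluate categorized clinical cut-off values using generalized estimating equation (GEE) analysis". It gives no measure of skewness that triggers this, no cut-off and no number of cut-offs, and it does not say which result decides if the two analyses disagree.

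Under Primary outcome, the self-reported measure is defined: "We will use a widely used measure of percent of prescribed dose taken during the preceding seven days". According to Schedule of events and assessments, the usual-care arm has self-report only, so this measure carries the between-arm comparison.

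Sample size calculation sizes Aim 2 on a standardized scale only: 55 per arm can "detect a difference as small as 0.29 in standardized unit of the outcomes (e.g., adherence to ART) between the two arms". No power is given for a categorized adherence outcome. The only adherence threshold in the article is the below-90% eligibility rule over 28 days in Table 1. Statistical analyses promises correction for multiple comparisons, with Bonferroni as an example.

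**The concern.** Hypothesis, sizing and test should refer to the same quantity. Here the first two refer to a mean, while the third may become a proportion above some threshold, depending on the shape of the data. That is a change of estimand, not only of method.

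The trigger is also foreseeable. A seven-day percentage cannot exceed 100%, and the Discussion says that self-report overestimates adherence, so values will tend to pile up near the top. The fallback may well be the analysis that gets run.

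The cut-offs ask different questions. If dosing is once daily (the article gives no dosing frequency), the scale has only the values 0/7 to 7/7, and 6/7 = 85.7%. Cut-offs of 80% and 85% then both mean at most one missed dose, and 90% and 95% both mean none missed. The mean, at most one missed and none missed can lead to different conclusions about efficacy. The trial is open-label, so blinding does not protect the choice.

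**Working it through.** **1. The plan's own figure.** Inputs from Sample size calculation: 55 per arm, 80% power, type I error 0.05, intra-subject correlation ρ = 0.1, and m = 3.5 data points on average out of 5.

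- SD of a subject's mean, in SD units: √[(1 + (m − 1)ρ)/m] = √(1.25/3.5) = 0.598.
- Detectable difference, two-sided: (1.960 + 0.842) × 0.598 × √(2/55) = 0.319.
- One-sided: (1.645 + 0.842) × 0.598 × √(2/55) = 0.283.
- Two-sided with all 5 points: √(1.4/5) = 0.529, which gives 0.283.

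So 0.29 is matched under a one-sided reading, or with five complete points. With 3.5 points and a two-sided test, 0.29 has 72% power. The section states sidedness only for Aim 1 ("a significance level of 0.05 using a two-sided two-sample t-test"). This is a separate matter. What counts here is that the figure is for a continuous outcome.

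**2. Does skewness invalidate the mean comparison?** Two null simulations were run, with 3,000 trials per setting and 55 per arm.

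- Seven-day binomial reports with logit-normal subject and visit effects, four post-baseline visits, 30% missing at random, cluster-robust standard errors, skewness about −0.6 to −1.4: the mean test rejects 4.6-5.6% of the time.
- Beta-distributed adherence, four visits, latent correlation 0.1, skewness about −1.0 to −1.25: the mean test rejects 4.4-5.4% of the time.

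The test keeps its size in both.

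**3. Power at a uniform shift of about 0.29 SD, low intra-subject correlation.**

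| Setting | Mean | Single cut-off |
|---|---|---|
| Binomial reports (0.287 SD) | 68% | 55% (at least 80%), 44% (at least 90%) |
| Beta-distributed (0.29 SD on the latent scale) | 69-71% | 46-60% (80, 85, 90 or 95%) |

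The losses run from roughly 10 to 24 points. With higher intra-subject correlation the gap narrows: 36-40% for the mean against 32-35% for a cut-off.

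**4. Analytic cross-check.** The relative efficiency of a dichotomized normal variable is φ(c)²/[p(1 − p)], where p is the share of readings on one side of the cut-off c. The article gives no share, so a range is shown. Power is two-sided at 0.29 with m = 3.5, where the undivided outcome has 72%.

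| Split | Efficiency | Power | Per arm to keep planned power (55/efficiency) |
|---|---|---|---|
| 50/50 | 0.637 | 53% | 87 |
| 70/30 | 0.576 | 49% | 96 |
| 80/20 | 0.490 | 43% | 113 |
| 90/10 | 0.342 | 32% | 161 |

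These losses exceed the simulated ones. The formula assumes an underlying normal variable and carries ρ = 0.1 over to the binary scale, which is slightly pessimistic.

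**5. Type I error of the switch.**

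- Switching to one cut-off when skewness pooled over arms passes an assumed trigger: 4.5-6.4%, near nominal.
- Uncorrected choice of the best of the mean, the 80% and the 90% cut-off: about 10-12%.
- Bonferroni over two cut-offs: 4.7-5.1%. Over the mean plus both cut-offs: 3.6-4.4%.

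**The case against.** The strongest reply has four parts.

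- **The mean model is not dropped.** The clause says that cut-offs will be evaluated. It does not say that the arm term in the mixed model is abandoned, and AIM 2 later repeats, without condition, that adherence will be modelled by arm over time. This stands: replacement is a natural reading but is not written. If both analyses are run, however, the article still does not say which one decides.
- **Trigger and cut-off are detail for the analysis plan.** A condensed article may leave both to a fuller document, so their absence alone is no fault. What the article does state is a data-dependent route from a mean to a proportion. That is a rule, and a later document would have to override it.
- **Error control is promised.** A reader might infer that the clause roughly doubles the false-positive rate. The documents do not support that. A trigger based on pooled shape carries no information about the arm contrast, and the calculation shows near-nominal error. The figure of about 10-12% needs the best of three tests to be reported without the correction promised in Statistical analyses, and nothing suggests that this is intended.
- **The power loss depends on the model.** It assumes a uniform shift. An effect concentrated at one cut-off could lose little or nothing. Part of the gap between 80% and the simulated 68-71% for the mean belongs to the 0.29 figure itself, not to dichotomizing.

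**Conclusion.** The point holds as a mismatch between hypothesis, sizing and test, with no deciding contrast named once the data are skewed. It is an inexpensive improvement to the plan, not evidence of an uncontrolled error rate.

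Its size is a loss of roughly 10 to 24 points of power if a cut-off becomes the deciding test, for a uniform shift of about 0.29 SD at low intra-subject correlation. At higher correlation the loss is a few points. This buys no validity, since the mean comparison already keeps its level under the skewness examined.

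The result rests on assumed adherence distributions, assumed cut-offs of 80-95%, and 55 per arm. Missing data at random and seven-dose reports were assumed in the binomial setting only. Two parts do not depend on these assumptions: the article sizes no categorized adherence outcome, and it does not say which analysis decides.

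**What to change.** - State in AIM 2 that the deciding test is the between-arm difference in mean self-reported percent adherence from the planned mixed model, whatever the skewness. Say which time points it covers; Sample size calculation counts baseline and weeks 4 to 16.
- Deal with skewness in the inference: cluster-robust or bootstrap standard errors, or a permutation test that respects the randomization strata.
- Report one dichotomized analysis by GEE as supportive only, at a cut-off fixed now. At least 90% would match the eligibility threshold in Table 1, although that threshold covers 28 days and, with once-daily dosing, 90% over seven days means no missed dose.

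A narrower repair would keep the switch but fix one cut-off and a numerical trigger judged blind to arm. That also settles the deciding test, but it leaves the power loss and the mismatch with the sizing.

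The cost is a change of wording and a few lines of analysis code. Sample size and data collection do not change. The sponsor gives up the option of making a cut-off result the main finding.
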